### Randomization and blinding

2.5

Patients meeting the criteria would be randomly assigned to treatment group (Danhong injection group) or control group (placebo group) in a 1:1 ratio through a randomization tool based on a central network. Random sequences were generated using SAS 9.3 software (SAS Institute, Cary, NC) by independent statisticians that were not involved in trial implementation or statistical analysis. The research assistant entered patient information on a tablet computer and was assigned a random number to complete the random assignment. The outcome of the assignment was unknown to the patients and principal investigator throughout the study. Because Danhong injection was different from 0.9% normal saline in color, we used opaque brown bag to seal the infusion bottle and used brown infusion set for infusion. A professional nurse prepared the medication in a dedicated infusion room and sealed the infusion bottle in a brown bag with only the patient's number on it, another nurse was responsible for completing the infusion according to the number. These programs would be implemented by 2 professional nurses, and they would be asked to sign a confidentiality agreement before the start of the study without being in contact with each other.

### Intervention measures

2.6

According to *2014 American College of Cardiology/American Heart Association Guidelines for the Diagnosis and Treatment of Non-ST-Segment Acute Coronary Syndrome*, all patients would receive dual antiplatelet therapy (aspirin 100 mg/d +clopidogrel 75 mg/d) and anticoagulant therapy (unfractionated heparin). And they would also receive statins, angiotensin converting enzyme inhibitors, beta-blockers, and nitrates according to the guidelines.^[18]^ All of these basic treatments will be detailed on the patient's medical record and CRF.

The treatment group was treated with Danhong Injection (Danhong Pharmaceutical Co., Ltd., Shandong, China), 40 ml/d combined with 0.9% normal saline, 250 ml/d intravenously, and the control group was treated with placebo (0.9% normal saline), 40 ml/d, combined with 0.9% normal saline, 250 ml/d, intravenously. All patients received standard treatment for 14 days.

When angina attacks, patients were instructed to take nitroglycerin tablets (Yimin Pharmaceutical Co., Ltd., Beijing, China), 0.5 mg/time, repeated every 5 minutes until angina relieved. Timing and dosage would be recorded in detail on the Case Report Form.

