## Introduction

1

Cardiovascular and cerebrovascular diseases are the main causes of death worldwide.^[1]^ According to WHO statistics, 17.9 million people died of cardiovascular diseases worldwide in 2016, accounting for 31% of the total global deaths, among which about 34% died of coronary heart disease.^[2]^ Coronary heart disease has become 1 of the diseases with the highest mortality rate in human beings and seriously endangers human physical and mental health.^[1]^ Angina pectoris of coronary heart disease is a syndrome caused by acute myocardial ischemia and anoxia,^[3]^ its pathogenesis is complex and generally related to epicardial coronary artery stenosis caused by atherosclerosis, reducing the coronary circulation of myocardial blood supply. And coronary microcirculation, imbalance between myocardial oxygen supply and metabolic oxygen demand are also important influence factors. Its molecular mechanism may involve vascular endothelial function, immune inflammation, thrombosis, lipid metabolism, oxidative damage, and other factors.^[4]^

At present, drug therapy for angina pectoris of coronary heart disease includes nitrates, calcium antagonists, antiplatelet aggregation, drugs that improve myocardial metabolism, drugs that stabilize atherosclerotic plaques and β-blockers, etc.^[5]^ Although some drugs take effect fast and the curative effect is distinct, but in the face of angina pectoris of coronary heart disease, which is a multi-pathway and multi-gene complex disease, the drugs still exist certain limitations.^[6]^ And clinical studies have found that traditional anti-myocardial ischemia therapy does not reduce cardiovascular adverse events, there are still 5% to 15% of patients with refractory angina pectoris attack.^[6,7]^

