#### Diagnostic basis

2.3.1

The diagnostic criteria for angina pectoris of coronary heart disease refers to *Nomenclature and criteria for diagnosis of ischemic heart disease*.^[15]^ The diagnostic criteria of TCM diseases and syndromes refers to *Diagnostic and therapeutic criteria of traditional Chinese medicine diseases*.^[16]^

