#### Inclusion criteria

2.3.2

Patients who meet the diagnostic basis of angina pectoris of coronary heart disease, and meet the requirements of coronary angiography or coronary angiography that there is at least 1 coronary artery stenosis with catheter stenosis ≥50%, and whose myocardial ischemia and ECG ST-T changes are confirmed by cardiac MRI or radionuclide myocardial perfusion imaging.Patients whose age ≥18 years, and ≤70 years;Patients who agree to participate in this study and signed informed consent.

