#### Exclusion criteria

2.3.3

Patients who have severe mental illness, severe cardiopulmonary insufficiency, severe arrhythmia, or other serious illness (such as tumor);Patients whose ALT, AST or Cr reaches 1.5 times of normal upper limit^[17]^;Patients who have other diseases that may increase the risk of bleeding, such as a history of bleeding in vital organs (such as cerebral hemorrhage and upper gastrointestinal bleeding), reduced platelet count, abnormal coagulation function, and recent active bleeding within the last 6 months;Women who are pregnant, preparing to pregnant or breastfeeding;Patients who are allergic to the drugs used in the study;Patients who have participated within the last 1 month or are currently participating in other clinical trials.

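### Section 2.6 gives every patient aspirin, clopidogrel and heparin under a non-ST-segment ACS guideline, but the entry criteria do not require that presentation

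*Protocol article*

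**What the plan says.** **Background treatment (2.6).** The protocol article fixes one antithrombotic regimen for everyone: "all patients would receive dual antiplatelet therapy (aspirin 100 mg/d +clopidogrel 75 mg/d) and anticoagulant therapy (unfractionated heparin". The sentence rests on a single source, the "2014 American College of Cardiology/American Heart Association Guidelines for the Diagnosis and Treatment of Non-ST-Segment Acute Coronary Syndrome". Statins, ACE inhibitors, beta-blockers and nitrates are added according to the guidelines. On recording, 2.6 says: "All of these basic treatments will be detailed on the patient's medical record and CRF".

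**Entry (2.3.1 to 2.3.3).** Section 2.3.1 defines the condition by an outside source: "The diagnostic criteria for angina pectoris of coronary heart disease refers to" a published nomenclature of ischemic heart disease. Section 2.3.2 then admits "Patients who meet the diagnostic basis of angina pectoris of coronary heart disease, and meet the requirements of coronary angiography" (at least one stenosis of 50% or more), "whose myocardial ischemia and ECG ST-T changes are confirmed by cardiac MRI or radionuclide myocardial perfusion imaging", aged 18 to 70. Section 2.3.3 excludes, among others, "Patients who have other diseases that may increase the risk of bleeding, such as a history of bleeding in vital organs", reduced platelets, abnormal coagulation and active bleeding in the last 6 months. Stable angina is not on the exclusion list.

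**The concern.** The two sections have different scope. Section 2.6 takes its regimen from guidance for one acute presentation and applies it to all participants, while the entry criteria are written for angina of coronary heart disease without that limit.

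Two things are at stake.

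- **Patient care.** A stable patient who meets 2.3.2 would be assigned two antiplatelet drugs and heparin, and the plan offers no indication for that patient. Bleeding is a risk the protocol itself takes seriously, since 2.3.3 screens for it. The Introduction also lists an anticoagulant action among the pharmacological effects of Danhong injection, which the treatment arm receives on top of the three drugs.
- **Whom the result describes.** The Abstract offers the result for angina of coronary heart disease in general, while background care is that of non-ST-segment ACS. Without a stated presentation, a reader cannot tell which population was studied.

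**Working it through.** No calculation decides this point. The check sets the sections side by side.

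| Place | What it fixes | Is an acute presentation required? |
|---|---|---|
| 2.3.1 Diagnostic basis | Angina defined by outside criteria | Not in the visible text; the source itself is not available |
| 2.3.2 Inclusion | Angina, stenosis of 50% or more, ischemia and ST-T changes, age 18 to 70 | No; no mention of unstable angina, ACS, rest pain or recent onset, and no time window on the ST-T changes |
| 2.3.3 Exclusion | Raised bleeding risk, severe comorbidity and others | No; stable angina is not excluded |
| 2.6 Intervention | Aspirin, clopidogrel and heparin for all | Only through the title of the cited guideline |

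1. Take a patient aged 60 with long-standing effort angina, one stenosis above 50%, ischemia with ST-T changes shown on perfusion imaging, and none of the listed exclusions. Nothing visible in 2.3.2 or 2.3.3 keeps this patient out.
2. Section 2.6 then assigns all three drugs. It makes no exception and gives no other basis.
3. Could the clinician simply adapt the regimen? Section 2.3.4 counts patients who change their medication, where this may affect the result, among the withdrawal cases. Leaving out heparin could be read as falling under that rule.
4. Number affected: enrolment is 55 × 2 = 110 (2.4). The share of stable patients is not given. The count could lie anywhere from 0 to 110, a range that says nothing beyond the trial's size, so no estimate is offered.
5. Effect on the comparison: 2.6 prescribes the same background care in both arms and allocation is random (2.5), so the mismatch introduces no bias between arms.
6. Effect on power: the inputs in 2.4 are the two LVEF means and standard deviations, α, β and drop-out. The mismatch alters none of them.

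**The case against.** The strongest reply is that the trial is meant for acute patients and the subtype was merely left unnamed. Several cues point that way. The Introduction says "Angina pectoris of coronary heart disease is a syndrome caused by acute myocardial ischemia and anoxia". Section 2.3.2 asks for ST-T changes. Sections 2.5 and 2.6 describe 14 days of intravenous treatment from a dedicated infusion room, with heparin. The outside criteria in 2.3.1 may also narrow entry. On that reading 2.6 and the entry criteria fit together.

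Much of this stands. It means that the number of stable patients may be zero, and that the text supports no stronger claim than a mismatch of scope. None of the cues, however, is stated as a condition of entry. The Introduction's sentence is background, the ST-T requirement has no time limit, and inferring the population from the guideline is circular because the guideline's fit is the question. If acute patients are meant, 2.3.2 still needs to say so.

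A second reply is that the safeguards suffice. The age cap of 70, the bleeding exclusions, stopping for severe adverse events (2.3.4) and adverse event recording (2.8) do limit the risk. They do not supply an indication for a patient outside the cited guideline.

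A third is that this is a condensed article. That carries limited weight, because both the entry criteria and the universal regimen are printed here.

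**Conclusion.** The point holds as a minor mismatch of scope: the mandatory regimen in 2.6 is wider than the basis cited for it, because 2.3.1 to 2.3.3 as written do not require a non-ST-segment ACS presentation. An eligible stable patient would receive heparin plus dual antiplatelet therapy with no stated indication. The conclusion assumes that the unseen criteria in 2.3.1 do not themselves restrict entry to acute patients.

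A reader might infer more, and the documents do not support it:

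- *That stable patients will be enrolled in some number.* No case mix is given, and the count may be zero.
- *That an excess of bleeding follows.* No bleeding rate is given, and 2.3.3 removes patients at known risk.
- *That the treatment comparison is biased or underpowered because of this.* Background care is common to both arms, and no sample size input changes.

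What remains is a gap in the justification of background care and an unclear target population.

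**What to change.** The documents do not show which population was intended, so the trial team should choose one of two edits.

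1. **If only acute patients are meant:** add to 2.3.2 that entry requires unstable angina or non-ST-segment ACS, and limit the conclusion to that population. This is the simpler edit and fits the cues above. Cost: a narrower population and possibly slower recruitment.
2. **If stable patients are intended:** reword 2.6 along these lines: *Unfractionated heparin and dual antiplatelet therapy will be given to patients presenting with unstable angina or non-ST-segment ACS, or with another documented indication.* Name the guideline that governs antithrombotic care for the others, so that the text does not become looser than it is now, and record presentation at baseline on the CRF. Cost: one extra CRF field, since treatments given are already recorded, and background care that varies between patients, though alike in both arms.

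Either edit is a protocol change and needs renewed ethics approval under 2.9.

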### Study design

2.1

This is a prospective, randomized, double-blind, placebo-controlled study of the effects of Danhong injection on cardiac function and lipid profile in patients with angina pectoris of coronary heart disease. Participants will be randomly divided into treatment group and control group, the treatment group will receive Danhong injection treatment, and the control group will receive placebo treatment. The patients will be followed up for 3 months after 14 days of continuous treatment. Flow diagram is shown in Figure 1, study schedule is shown in Table 1. This protocol followed the latest Consolidated Standards of Reporting Trials 2017 and Standard Protocol Items: Recommendations for Interventional Trials 2013 statement.

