#### Shedding criteria and management

2.3.4

Patients who appear severe adverse events or other complications and special physiological changes. The trial should be stopped and corresponding treatment should be given according to the judgment of the investigator;If the subject's condition does not improve or even deteriorate to a certain extent within a certain period of time, although the required follow-up had not been completed, the subject should be withdrawn from the study and received other effective treatments in order to protect the subject;Patients who have poor compliance, change medications or add non-prescribed medications, which may affect the result of the study;Patients who are unwilling or impossible to continue the clinical trial for any reason, and suspend the test by requesting the investigator to withdraw from the test;Patients who are misdiagnosed, or accidentally included without meeting the inclusion and exclusion criteria.

For patients who dropped out of the trial or lost to follow-up, researchers should take active measures to complete the last test as far as possible, so as to analyze its efficacy and safety, and take corresponding treatment measures. All shedding cases should be recorded on the case report form (CRF), and filled in the cause.

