### Outcomes

2.7

Cardiac function: Color Doppler ultrasonography (GE-VIVID7, US) was used before and after treatment and during follow-up time to detect patient's left ventricular end-diastolic diameter, left ventricular end-systolic diameter, and LVEF.Blood lipid levels: Fasting vein blood was collected in the morning before and after treatment and during follow-up time, and automatic biochemical analyzer (HITEC-7100, Japan) was used to detect blood lipid indexes of the patients, including total cholesterol; triacylglycerol; low density lipoprotein cholesterol; high-density lipoprotein cholesterol.The number of weekly attacks of angina pectoris; total amount of nitroglycerin tablets taken during the study period.

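### Lipids are a named objective and every patient gets guideline statins, but statin status at entry is neither constrained, named as a stratum nor adjusted for, which may cost the lipid comparison precision

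*Protocol article*

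**What the plan says.** All references are to the protocol article.

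- **Objective.** Section 2.1 describes a study of the "effects of Danhong injection on cardiac function and lipid profile in patients with angina pectoris of coronary heart disease", so lipids stand beside cardiac function.
- **Measurement.** Section 2.7 lists total cholesterol, triacylglycerol, LDL-C and HDL-C: "Fasting vein blood was collected in the morning before and after treatment and during follow-up time". Table 1 places the draws at baseline, week 2 and month 3.
- **Background treatment.** Section 2.6 says of all patients that "they would also receive statins, angiotensin converting enzyme inhibitors, beta-blockers, and nitrates according to the guidelines". It adds "All patients received standard treatment for 14 days", and "All of these basic treatments will be detailed on" the medical record and CRF.
- **Entry.** Sections 2.3.2 and 2.3.3 contain no statin or lipid condition. Table 1 puts eligibility, consent, allocation and first treatment in the one baseline column and shows no run-in.
- **Medication changes.** Section 2.3.4 lists as withdrawals patients who "change medications or add non-prescribed medications, which may affect the result of the study". This applies after entry and is not an eligibility rule.
- **Allocation.** Section 2.5 assigns patients "in a 1:1 ratio through a randomization tool based on a central network" and names no stratification factor.
- **Analysis.** Section 2.10 gives an independent-sample t test, or Mann-Whitney U for skewed data. It names no covariate and does not say whether change or post-treatment values are compared.

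**The concern.** Statins act directly on the lipid outcomes, and everyone is to receive them. A patient already on a statin has a baseline lipid value measured on treatment. A patient who first receives one at entry has a baseline measured off treatment and can be expected to fall further by week 2 and month 3. The article allows both kinds of patient in and does not separate them in allocation or in the stated test.

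What is at stake is precision. A mixture of the two kinds of patient widens the spread of lipid change, and the arms may by chance hold different shares of starters. The sample size in section 2.4 rests on LVEF alone, so nothing in the article shows that the lipid comparison has precision to spare. The CRF will hold the background treatment, but section 2.10 gives that record no role.

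**Working it through.** **The plan's own figure.** Section 2.4 gives LVEF 53.13 ± 6.18 against 49.78 ± 5.78, one-sided α 0.025 and power 0.80. The difference is 3.35 and the pooled SD is sqrt((6.18² + 5.78²)/2) = 5.98. The normal approximation gives n = 2 × (5.983 × (1.960 + 0.842)/3.35)² = 50.1, so 51 per group. The plan states 49, which is close. Allowing for 10% drop-out, 49/0.9 = 54.4, so 55, as stated. Statin status does not enter this calculation. No effect, SD or sample size is given for any lipid.

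**Inputs for lipids.** From the article: 49 evaluable patients per group. Assumed, because the article gives none of them: share of starters p = 0.3-0.7; extra LDL-C fall in starters e = 0.8-1.2 mmol/L; SD of change within each kind of patient s = 0.7 mmol/L.

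**Variance of change if statin status is ignored:** s² + e² p(1−p).

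- Low end (e = 0.8, p = 0.3 or 0.7): 0.49 + 0.64 × 0.21 = 0.624; ratio to 0.49 = 1.27.
- High end (e = 1.2, p = 0.5): 0.49 + 1.44 × 0.25 = 0.850; ratio = 1.73.
- Equivalent loss of sample: 1 − 0.49/0.624 = about 21%, to 1 − 0.49/0.850 = about 42%.

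**Effect on the detectable difference** (two-sided 0.05, 80% power, 49 per group): 2.80 × SD × sqrt(2/49).

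- No mixture: 2.80 × 0.70 × 0.202 = 0.40 mmol/L.
- With mixture: SD sqrt(0.624) = 0.790 gives 0.45; SD sqrt(0.850) = 0.922 gives 0.52 mmol/L.

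**Chance imbalance.** The 95% range for the difference in starter share is 1.96 × sqrt(2p(1−p)/49), which is 18 percentage points at p = 0.3 or 0.7 and 20 at p = 0.5. Multiplied by e, this is 0.18 × 0.8 = 0.15 up to 0.20 × 1.2 = 0.24 mmol/L. It is not a second harm: it is the source of the extra variance above.

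**Is there bias?** A simulation of the unadjusted t test (40,000 runs, 49 per group, within-type SD 0.8, 25-50% starters, extra fall 1.0-1.5 mmol/L, all assumed) kept the type I error at 4.8-5.1%. Power for a true difference of 0.46 mmol/L fell from 81% to 54-70%.

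**Sensitivity.** With SD 0.6-1.0, 25-50% starters and an extra fall of 0.5-1.5 mmol/L, the variance ratio runs from 1.05 to 2.56.

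**Post-treatment values.** If these are compared instead of changes, e is replaced by the gap that remains between the two kinds of patient once all are on statins. If their values converge, that gap, and with it the added variance, goes to zero.

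**The case against.** The strongest reply is that both arms receive the same background treatment under randomisation and blinding. Statin response is then noise, and a significant lipid difference remains a valid result for adding Danhong to standard care, which the Discussion says is the setting studied. This stands. A reader might infer that a lipid result could not be attributed to Danhong; the design does not support that.

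A reader might also infer that statins are started or changed together with study drug. The article does not say so. It leaves earlier use, start date, agent and dose open. A 14-day standard treatment over the same 14 days as study drug makes new starts plausible, but no share can be read from the text.

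Nor is it shown that statin response would swamp a Danhong effect. With SD 0.7 the significance threshold is 1.96 × 0.7 × sqrt(2/49) = 0.28 mmol/L, above the 0.15-0.24 mmol/L that chance imbalance reaches at its 95% limit. The variance figures also apply to change scores, which section 2.10 does not specify.

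Finally, strata and covariates may sit in a full protocol or SAP that is not shown, so their absence alone is not a fault. What remains is what the article does state: complete-looking eligibility lists without a statin condition, and a named test that takes no covariate. The CRF record and the withdrawal rule help, but neither separates established users from starters at entry.

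**Conclusion.** The point holds as one of precision. The stated lipid analysis ignores a foreseeable source of variation that the CRF already captures. If a material share of patients are new to statins at entry, and if changes are compared, the variance of LDL-C change rises about 1.27-1.73 times under the stated assumptions. The detectable difference then rises from about 0.40 to 0.45-0.52 mmol/L. If few patients are starters, or post-treatment values are compared and converge, the loss may be small. The type I error is not affected, and neither is the LVEF-based sample size. This is a low-cost improvement to a named objective; the lipid comparison is valid without it.

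**What to change.** In section 2.10, replace the unadjusted lipid test with a linear model for each lipid outcome containing:

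- treatment;
- the baseline value of that lipid;
- statin status at entry (established, or new or recently changed), taken from the CRF with the definition fixed in advance;
- the interaction of baseline value with statin status.

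The interaction is needed because a baseline measured on a statin and one measured off it predict the later value differently, so baseline alone is not enough. State also whether change or the post-treatment value is reported; with baseline in the model the treatment estimate is the same either way.

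If randomisation has not begun, add statin status as a two-level stratum to the central randomisation in section 2.5. If it has begun, the model alone still deals with chance imbalance. Report the established-statin subgroup as supportive only, since it is a smaller part of a trial sized on LVEF.

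The cost is one more stratum to manage, a clear CRF definition and a few model terms. No patient's treatment changes.
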